5.1 Inclusion Criteria

- - Male or female, 2 to 59 months of age.
  - History of cough <14 days or difficult breathing with chest-indrawing.
  - Ability and willingness of child’s caregiver to provide informed consent and to be available for follow-up for the planned duration of the study, including accepting a home visit if he/she fails to return to KCH for a scheduled study follow-up visit.

5.2 Exclusion Criteria

- If chest-indrawing observed at screening resolves after bronchodilator challenge, among those with wheeze at screening.
- Severe respiratory distress (e.g., grunting, nasal flaring, head nodding, or severe chest-indrawing).
- Presence of WHO IMCI danger signs including: lethargy or unconsciousness, convulsions, vomiting everything, or inability to drink or breastfeed.
- Hypoxia (SaO2 < 90% on room air, as assessed by a Lifebox pulse oximeter).
- Stridor when calm.
- HIV-1 seropositivity or HIV-1 exposure, assessed as follows:
  - An HIV-positive result upon rapid antibody test will exclude any child from this study.
  - If a child is less than 12 months or age with a positive rapid test result, the child will be referred to receive additional confirmatory HIV testing (e.g., dried blood spot filter paper test) and follow-up from KCH staff, as per standard of care. Even if the confirmatory HIV testing subsequently shows that child is HIV-negative, he or she will remain excluded from the study.
  - If a child is less than 24 months of age and has an HIV-negative result upon rapid antibody test, the child’s biological mother’s HIV status will need to be assessed. If the mother is HIV-positive, the child will be excluded. If the mother has a documented HIV-negative test result from within the past 6 weeks, the child will be included. If the mother does not have documentation of an HIV-negative test result, she will be tested via rapid antibody testing to determine the child’s eligibility for this study.
  - If a child is over 24 months of age, an HIV-negative rapid antibody test is required for inclusion in the study.
  - Note: If a child has documentation of an HIV-negative test result from within the past 6 weeks, that test result will be used for the child’s eligibility assessment according to the algorithm described above.
- Severe acute malnutrition (i.e., weight for height/length < -3 SD, mid-upper arm circumference <115 mm, or edema).
- Possible tuberculosis (coughing for more than 14 days).
- Severe anemia, classified by WHO pocketbook guidelines (i.e., severe palmar pallor or hemoglobin <8.0 g/dL)
- Severe malaria, classified by WHO pocketbook guidelines (e.g., positive mRDT with any danger sign, stiff neck, abnormal bleeding, clinical jaundice, or hemoglobinuria)
- Known allergy to penicillin or amoxicillin.
- Receipt of an antibiotic treatment in the 48 hours prior to the study based on caregiver’s self-report and/or documentation in child’s medical record.
- Hospitalized within 14 days prior to the study.
- Living outside Lilongwe urban area, the study catchment area.
- Any medical or psychosocial condition or circumstance that, in the opinion of the investigators, would interfere with the conduct of the study or for which study participation might jeopardize the child’s health.
- Any non-pneumonia acute medical illness which requires antibiotic treatment per local standard of care.
- Participation in a clinical study of another investigational product within 12 weeks prior to randomization or planning to begin participation during this study.
- Prior participation in an Innovative Treatments in Pneumonia study during a previous pneumonia diagnosis.

Once a child is enrolled in the study, the staff will collect further data such as baseline characteristics, vital signs, vaccination history and additional socio-economic information. Caretakers will bring enrolled children in for follow-up visits on days 2, 4, 6 and 14. Upon follow-up, study staff will collect information on medical history since the previous visit, study product adherence and results from the physical exam.

Statisticians will have access to all appropriate study visit data on both enrolled patients and screened patients who were not enrolled.

*5.3 Subgroups*

Though listed in the protocol as secondary endpoints, we will examine the primary endpoint of treatment failure by day 6 in three specific subgroups:

1. Proportion of children with treatment failure among those testing positive for malaria by rapid diagnostic testing (mRDT) at baseline or outcome assessment (overall).
2. Proportion of children failing treatment among those with wheeze at baseline during screening (prior to administration of bronchodilators).
3. Proportion of children failing treatment among those children 2-12 months, 13-35 months, and 36-59 months of age at baseline.
4. Proportion of enrolled children failing treatment among those with oxygen saturation <93% by pulse oximetry at baseline.
5. Proportion of children failing treatment among those with MUAC-defined moderate malnutrition (11.5-13.5cm).
6. Proportion of children failing treatment among those with very fast breathing for age (>70 breaths per minute for 2–11 months, >60 breaths per minute for 12–59 months)

The same treatment failure definition as above will be used for these subgroups analysis. Subgroup classification will be obtained from the screening data.

Additional subgroups not defined in either the approved protocol or statistical analysis plan will be considered post-hoc. Statisticians will keep a list of post-hoc analysis requested by investigators during the study duration.

1. **ENDPOINTS AND COVARIATES**

*6.1 Primary endpoint*

The primary endpoint will be the proportion of children failing treatment, defined as the development of any of the following before or on day 6:

- - - - WHO Integrated Management of Childhood Illness (IMCI) danger signs
      - Severe respiratory distress (e.g., grunting, nasal flaring, head nodding, or severe chest-indrawing).
      - Oxygen saturation < 90% by pulse oximetry
      - Vomiting within 30 minutes of 3 or more scheduled (i.e., not repeat) dose administrations of study product
      - Change in antibiotics prescribed by a study clinician (e.g., switch to a second-line antibiotic or prescription for onset of a co-infection)
      - Death

At or after initial hospitalization discharge assessment (between 42 and 60 hours post-enrollment):

- - - - Documented axillary temperature > 38 ºC with chest-indrawing

At day 6 outcome assessment:

- - - - Documented axillary temperature > 38 ºC
      - Chest-indrawing

The primary endpoint will be calculated from day 2, 4, 6 follow-up forms. The presence of any of the above criteria at any point prior to day 6 will constitute treatment failure. In addition to the overall treatment failure rate by day 6, we will also examine the treatment failure rates at 2 and 4 for both treatment arms.

Covariates for primary analysis: In addition to the treatment variable, the primary analysis will include (be adjusted for) the following covariates: age (2 months up to 12 months, 12 months up to 3 years, 3 years up to 5 years) and site (Bwaila District Hospital and Kamuzu Central Hospital). Of note, these are the same variables that are used for stratifying randomization. In addition, we will adjust for gender, as gender has been shown to be related to pneumonia mortality[1].

*6.2 Secondary endpoints*

The trial has the following several secondary endpoints

1. Proportion of children with clinical relapse between treatment failure assessment and day 14 follow-up visit among all children without treatment failure before or on day 6.
2. Proportion of children with either treatment failure or clinical relapse before or on day 14 (among all randomized children).
3. Proportion of children with AEs and SAEs.
4. Proportion of children with treatment failure among those testing positive for malaria by rapid diagnostic testing (mRDT) at baseline (overall).
5. Proportion of enrolled children failing treatment among those with wheeze during screening (identified prior to administration of bronchodilators).
6. Proportion of enrolled children failing treatment among those with oxygen saturation <93% by pulse oximetry at baseline.
7. Proportion of children failing treatment among those with MUAC-defined moderate malnutrition (11.5-13.5cm).
8. Proportion of children failing treatment among those with very fast-breathing for age (>70 breaths per minute for 2–11 months, >60 breaths per minute for 12–59 months).
9. Proportion of children failing treatment by age at baseline.
10. **STATISTICAL METHODOLOGY**

*7.1 Design*

The study will include 2,000 children aged 2 to 59 months. Children will be randomized to receive oral amoxicillin for 5 days (control) or 3 days + 2 days placebo (treatment). Treatment will be block randomized (with concealed block size) to ensure a 1:1 ratio of intervention and control. Randomization will be stratified by age group (2 up to 12 months, 12 up to 3 years, 3 years up to 5 years) and site (Bwaila District Hospital and Kamuzu Central Hospital).

*7.2 Interim analysis* We planned two interim analyses after about one-third and two-thirds of children have been enrolled. The seqDesign[2] software was used to determine the appropriate non-inferiority and futility stopping boundaries at each analysis. We assumed a one-sided test with an alpha=0.025, sample size = 1900 (assuming 5% loss to follow-up in each of the arms), a Pocock design for early inferiority and O’Brien-Fleming for early non-inferiority stopping boundaries and a 1.5 relative non-inferiority boundary.

The maximum true failure rates at both the interim analyses and final analysis for the 3-day group for which the 95% CI excludes the non-inferiority margin for various 5-day treatment group failure rates are provided in Table 1 below.

Table 1. Maximum true failure rates for the 3-day treatment arm beyond which stopping for early non-inferiority will be considered

| 5-day failure rate | Non-inferiority bound | Max 3-day failure rate, 1st interim analysis | Max 3-day failure rate, 2nd interim analysis | Max 3-day failure rate, final analysis |
| --- | --- | --- | --- | --- |
| 7.0% | 10.5% | 4.0% | 7.2% | 8.3% |
| 8.0% | 12.0% | 5.0% | 8.5% | 9.7% |
| 9.0% | 13.5% | 6.0% | 9.8% | 11.0% |
| 10.0% | 15.0% | 7.1% | 11.1% | 12.4% |
| 11.0% | 16.5% | 8.2% | 12.4% | 13.7% |
| 12.0% | 18.0% | 9.4% | 13.7% | 15.1% |

The minimum true failure rates for the 3-day treatment group for which futility is considered for various 5-day treatment group failure rates are provided below.

Table 2. Minimum true failure rates for the 3-day treatment arm where futility will be considered

| 5-day failure rate | Min 3-day failure rate, 1st interim analysis | Min 3-day failure rate, 2nd interim analysis | Min 3-day failure rate, final analysis |
| --- | --- | --- | --- |
| 7.0% | 10.2% | 8.9% | 8.3% |
| 8.0% | 11.7% | 10.3% | 9.7% |
| 9.0% | 13.2% | 11.7% | 11.0% |
| 10.0% | 14.6% | 13.1% | 12.4% |
| 11.0% | 16.1% | 14.5% | 13.7% |
| 12.0% | 17.6% | 15.9% | 15.1% |

Figure 1 shows the maximum true failure rate in the 3-day treatment group in reference to various possible failure rates in the 5-day treatment group and a 1.5 relative non-inferiority margin (50% relative increase in failure rate) that would result in a 95% confidence interval at maximum enrollment which excludes the non-inferiority margin. The figure also indicates the power the study has to show non-inferiority if the failure rates are exactly the same in the two treatment groups for various possible failure rates. Of note, the estimated power is adjusted for a 5% loss to follow-up rate in each of the arms. This is considered conservative with respect to the multiple imputation procedure that will be used to account for missing outcome values.

**Figure 1.** Chest-indrawing pneumonia failure rates

Note:

- Blue, solid circles, blue number below: Potential failure rates for the 5-day treatment group.
- Blue, solid circles, blue number above: Power to detect the alternative of exactly equal failure rates in both treatment groups
- Green, hollow squares: Non-inferiority margins (depending on assumed failure rate in the 5-day treatment group.

Hollow, red circles: Maximum true failure rate for the 3-day treatment group observed at maximum enrollment of 2,000 children (1,000 children in each control and treatment groups and assuming 5% loss to follow-up in each of the groups resulting in 1,900 children with complete outcome data for the primary analysis) for which the 95% confidence interval excludes the non-inferiority margin. For example, for a failure rate of 8% in the 5-day treatment group (assumed for the chest-indrawing pneumonia), the true failure rate in the 3-day treatment group can be 9.7% (1.7% above the control group) and can still rule out with high confidence a failure rate of 12% in the 3-day treatment group.

The DSMB will consider recommending to stop the study prior to maximum enrollment if they determine early non-inferiority, early inferiority, or safety concerns.

Early non-inferiority will be considered if the 3-day failure rate is lower than the rates provided in Table 1 for a given 5-day treatment failure rate. For instance, if the 5-day treatment rate at the first interim analysis is 7%, then early non-inferiority will be considered if the 3-day failure rate is less than 4.0%.

Early futility will be considered if the 3-day failure rate is higher than the rates provided in Table 2 for a given 5-day treatment failure rate. For instance, if the 5-day treatment rate at the interim analysis is 7%, then early futility will be considered at the first interim analysis if the 3-day failure rate is higher than 10.2%.

- 1. *Final analysis*

For the primary outcome, we will estimate the failure rate difference and 95% CI between the 3-day and 5-day amoxicillin DT treatment groups after adjustment for age, 2 up to12 months, 12 months up to 3 years, 3 years up to 5 years, site (Bwaila District Hospital and Kamuzu Central Hospital) and gender (precision variable[1]). Since estimates are expressed in rate differences we will run a linear regression model with treatment arm as predictor (3-day vs. 5-day), failure rate (yes vs. no) as outcome and age, site and gender as covariates using robust standard errors and calculate a 95% CI. We will use a 1.5 relative non-inferiority margin. If the failure rate in the 5-day arm is 7%, the non-inferiority margin will be 10.5% (=7%*1.5). With a 5% failure rate the non-inferiority margin will be 7.5% (=5%*1.5).

To account for anticipated loss to follow-up or study withdrawal we will use multiple imputations for any missing outcome data. We will then perform sensitivity analyses to assess how the results might change with varying imputation assumptions. More information is provided in section 8 below.

1. **HANDLING OF MISSING DATA AND OTHER DATA CONVENTIONS**

We have estimated that loss to follow-up or study withdrawal will be 5%. Children lost to follow-up cannot be classified as improved or treatment failures at the missed visit. We will use multiple imputations for any missing outcome data. The imputations will be performed separately for each treatment group and cohort using multiple (20) hotdeck imputations and other information as described below. Multiple imputation estimates will be combined using Rubin’s approach[3].

Specifically, for each episode that is missing outcome data, we will create a subset of episodes that match exactly on treatment arm and gender while matching on age category, highest educational level achieved by the mother (none, primary, secondary, tertiary, while combining these categories for categories with less than 5% of participants, if needed, unknown education level will be multiply imputed, independent from outcome imputation) and adherence information (all combinations of categories for

a) days 1-3: no missing doses, 1-3 missing doses, 4-6 missing doses and

b) days 4-5: no missing doses, 1-2 missing doses, 3-4 missing doses,

unknown dosing information will be conservatively imputed as “not taken” for the 3 day arm and similar to patients where dosing is available for the 5-day arm). We will then randomly select one episode from the corresponding subset with complete information and use its values to replace the entire episode with missing outcome data.

We will repeat this process for each episode missing outcome data and calculate failure rates for both treatment arms using the imputed outcome. We will repeat this 20 times and determine the mean failure rates for each treatment arm. The difference between the mean failure rates will be calculated. Noninferiority bounds as listed in 7.2 will be consulted.

1. **SENSITIVITY ANALYSIS**

We will perform sensitivity analyses to assess how our results might change if the imputation assumptions are changed in a reasonable way, informing the robustness of the primary analysis result. We will perform complete case analysis as one form of sensitivity analysis.

1. **PROGRAMMING PLANS**

All data cleaning and programming will be done in R[4].

*10.1 DSMB Tables*

Data tables will be exported from R to Excel in the form of raw data. Raw data files will then be linked to a formatted Excel file and turned into PDF. Draft DSMB Open Session tables will be sent to appropriate clinical and statistical staff prior to the DSMB meeting and will use dummy randomization for the treatment arms. After finalizing content of DSMB tables, real randomization will then be used for the DSMB meeting.

*10.2 Manuscript tables*

Data tables will be exported from R to Excel in the form of raw data. Raw data files will then be linked to a formatted Excel file. Appendix A displays tables that will be considered for inclusion in the primary manuscript.

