## Screening

Screening procedures are conducted by study staff to determine eligibility for enrollment in the study. All inclusion/exclusion criteria must be assessed on presentation. The following procedures are performed for screening:

- - Provide information on the study
  - Obtain written informed consent for screening
  - Assign participant identification (ID) number
  - Collect demographic and address information
  - Collect medical history
  - Assess all eligibility criteria, including respiratory rate, chest-indrawing and pulse oximetry assessments (if not already documented in the medical record from that day) as well as a targeted physical examination
  - Perform malaria rapid diagnostic testing (mRDT). Those who are found to have malaria will receive appropriate antimalarial treatment using artemisinin-based combination therapy in addition to the randomly assigned treatment for pneumonia
  - Perform HIV rapid antibody testing if HIV status unknown
  - Perform hemoglobin test (HemoCue®) for anemia

Note that if a child presents with wheezing (audible or auscultatory), study staff will administer a trial of rapid acting inhaled bronchodilator for up to three times, 15-20 minutes apart. Study staff will then assess for fast-breathing and chest-indrawing again to determine the child’s eligibility for this study.

All screening procedures will be conducted by study staff, with the possible exception of the HIV rapid antibody test. HIV testing may be performed by either study staff or a team at KCH or BDH specially trained and experienced in pediatric HIV counseling and testing, whichever will reduce wait times for potential study participants and minimize disruption in regular care provision at KCH or BDH. Caregivers will be informed of all screening results during the screening visit, regardless of the eligibility status of their child.

For those children who are not eligible, study staff will inform the caregiver(s) that their child will not be able to participate in the study and will receive standard care at KCH or BDH instead. Children less than 12 months of age or breastfeeding who are excluded based on an HIV-positive rapid antibody test result will be referred for confirmatory testing (e.g., dried blood spot filter paper test).

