## Analytical Methodology for Final Analyses

We expect the project to produce evidence for chest-indrawing pneumonia that supports the effectiveness of 3 days of amoxicillin DT treatment to be non-inferior to 5 days of amoxicillin DT treatment.

We anticipate that some children may not return for their scheduled follow-up visits if no specific measures are taken to encourage more complete follow-up. In addition to appointment reminders and counseling caregivers on the importance of completing follow-up, study staff will provide incentives and transportation costs to minimize missing outcome data. For those children who do not return for their scheduled follow-up visits, study staff will conduct home visits the next day to assess the outcome. Even with these measures in place, we have estimated the loss to follow-up to be 5%. Children lost to follow-up cannot be classified as improved or treatment failures at the missed visit. We will use multiple imputations for any missing outcome data and perform sensitivity analyses to assess how our results might change if the imputation assumptions are changed in a reasonable way, informing the robustness of the primary analysis result. We will perform complete case analysis as one form of sensitivity analysis. The imputations will be performed separately for each treatment group and cohort using multiple (20) hotdeck imputations and adherence information as well as child’s age, gender, literacy status of the caregiver, and number of children in the household.

For the primary outcome, we will estimate the difference in failure rate between the 3-day and 5-day amoxicillin DT treatment groups (after adjustment for age, 2 up to 12 months, 12 up to 36 months and 36 up to 59 months) and calculate a 95% CI. The 3-day treatment will be considered non-inferior to the 5-day treatment group if the upper level of the 95% confidence interval excludes a relative increase in failure rate of 50% (factor of 1.5).

To address potential misclassification of eligibility and outcome, we plan to include sub-studies to validate eligibility and outcome in 10% of randomly selected children. For more details on potential misclassification and associated analyses, refer to the SAP.

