      1. To determine whether 3 days of treatment with oral amoxicillin DT in HIV-negative children 2 to 59 months of age with chest-indrawing pneumonia is as effective as 5 days of treatment.
   2. Secondary Objectives
      1. To determine whether the intervention arm has equivalent rates of treatment relapse as the control arm among those without treatment failure before or on day 6.
      2. To determine whether the intervention arm has equivalent rates of combined treatment failure and relapse before or on day 14 as the control arm.
      3. To determine whether the intervention arm has equivalent rates of adverse events (AEs) and serious adverse events (SAEs) as the control arm.
      4. To investigate whether there may be a differential treatment response in children who test positive for malaria at baseline. This information will be useful to plan further childhood pneumonia and malaria integrated interventions in similar settings.
      5. To determine whether there is a differential treatment response in enrolled children with wheeze during screening (identified prior to any bronchodilator administration).
      6. To determine whether there is a differential treatment response in enrolled children with an oxygen saturation level <93% by pulse oximetry at baseline.
      7. To determine whether there is a differential treatment response in enrolled children with mid-upper arm circumference (MUAC)-defined moderate malnutrition at baseline (11.5-13.5cm).
      8. To determine whether there is a differential treatment response in enrolled children with very fast-breathing for age at baseline (>70 breaths per minute for 2–11 months, >60 breaths per minute for 12–59 months).
      9. To determine whether there is a differential treatment response by age.
2. **DESIGN**

This project involves a double-blinded, randomized, non-inferiority trial in children 2-59 months of age from a malaria-endemic setting in Malawi comparing the effectiveness of 3-day to 5-day amoxicillin DT treatment for chest-indrawing, community-acquired pneumonia (ITIP2).

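### The primary model adjusts for age band, site and gender but leaves out recorded baseline measures, including two endpoint components, and so forgoes a little precision

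*Combined protocol and SAP*

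**What the plan says.** SAP 6.1 lists treatment, age band and site as model terms, describes age and site as the randomization strata, and then adds gender: "In addition, we will adjust for gender, as gender has been shown to be related to pneumonia mortality". SAP 7.3 calls gender a precision variable and specifies a linear regression of failure on arm, with "age, site and gender as covariates using robust standard errors". Protocol 5.1 (Final Analyses) has age alone: "after adjustment for age, 2 up to 12 months, 12 up to 36 months and 36 up to 59 months".

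The trial records more than this at baseline. Protocol 4.6 (Screening) includes "respiratory rate, chest-indrawing and pulse oximetry assessments" and a malaria rapid test. The enrollment visit adds vital signs and MUAC. Wheeze is noted before any bronchodilator. SAP Appendix A, Table 1 tabulates axillary temperature, saturation and respiratory rate by arm.

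The SAP uses most of these only to define subgroups. For example, one secondary objective in SAP 2 concerns children with an "oxygen saturation level <93% by pulse oximetry at baseline". Temperature is used only descriptively.

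**The concern.** By naming a precision variable, the SAP has accepted covariate adjustment for efficiency. The remaining question is which covariates to use. Gender is supported by a mortality reference, and nothing in the documents ties it to day 6 failure. Baseline saturation and temperature have a structural link to that endpoint: saturation below 90% at any time to day 6 is failure, and so is a temperature above 38 ºC at day 6. A child may enter with a saturation of 90% to 92%, close to a failure threshold, and no exclusion criterion limits temperature.

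At stake is the width of the interval compared with the non-inferiority margin. A covariate set fixed in advance also allows adjustment for whatever imbalance arises. The same adjustment chosen after the arms are compared would be open to challenge.

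**Working it through.** **Inputs from the documents.** 950 evaluable children per arm, 8% failure in both arms, an absolute margin of 4.0 points and stated power of 88% (protocol 4.5); one-sided alpha 0.025 and two interim looks (SAP 7.2); equal numbers of boys and girls (protocol 4.3).

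**Assumed, because the documents are silent.** How well gender or any baseline measure predicts treatment failure.

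**1. The plan's power figure.** SE = √(2 × 0.08 × 0.92 / 950) = 0.01245. Power = Φ(0.04/0.01245 − 1.96) = Φ(1.25) = 89.5% for a fixed design. Simulating three looks with the bounds in SAP Tables 1 and 2 gives 87.5%. The stated 88% therefore reproduces with no gain from covariates. The half-width of the 95% interval is 1.96 × 1.245 = 2.44 points.

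**2. Gender.** For a binary covariate with prevalence π and failure risks p₁ and p₀, R² = π(1−π)(p₁−p₀)² / (0.08 × 0.92).
- Risk ratio 1.2 (7.27% vs 8.73%): 0.25 × 0.01455² / 0.0736 = 0.07%.
- Risk ratio 1.5 (6.4% vs 9.6%): 0.25 × 0.032² / 0.0736 = 0.35%.

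**3. One binary severity marker, same formula.**
- Prevalence 10%, risk ratio 1.5: 0.18%, less than gender at that ratio.
- Prevalence 10% to 20%, risk ratio 2: 0.65% to 0.97%.
- Prevalence 10% to 20%, risk ratio 3: 2.2% to 2.8%.

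The ranking against gender thus depends on figures the documents do not give.

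**4. Several covariates together.** Take a normal risk score on the logit scale with mean risk 8% and SD 0.40, 0.55 or 0.75. This gives an AUC of 0.61, 0.65 or 0.70. The planned model is linear, so R² = cov(risk, standardised score)² / 0.0736. The variance of the treatment effect is multiplied by (1 − R²). Equivalent extra children = 1,900 × R²/(1 − R²).

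| Assumed AUC | Linear R² | Extra children | Fixed-design power | Half-width (points) |
|---|---|---|---|---|
| none added | 0 | 0 | 89.5% | 2.44 |
| 0.61 | 1.15% | 22 | 89.8% | 2.43 |
| 0.65 | 2.12% | 41 | 90.1% | 2.41 |
| 0.70 | 3.78% | 75 | 90.6% | 2.39 |

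**5. Starting from the stated 88%.** Φ((1.175 + 1.96)/√(1 − R²) − 1.96) gives 88.4%, 88.7% and 89.2%.

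These gains are upper figures for each AUC, because they treat all of the R² as additional to age, site and gender. Respiratory rate overlaps with age: the plan's own cut-offs for very fast breathing differ by age.

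**The case against.** The plan's choice is legitimate: the factors it declares as strata plus one prespecified, referenced covariate. Nothing in it is invalid, and the gain from changing it is small and rests on assumed AUCs. That stands, and it makes this an optional improvement.

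Two practical objections also stand, but they bear on the fix. SAP 8 imputes missing outcomes by matching on arm, gender, age, maternal education and adherence, with no severity measure. Because the donor's values replace the whole episode, the larger model would still run, but the matching set needs a check. Added covariates would also tighten only the regression interval. The interim tables, and the comparison of mean imputed rates with those bounds in SAP 8, use failure rates by arm and would not change.

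Three stronger readings are tempting and are not supported:
- **That the omitted measures predict failure better than gender.** No section reports or ranks any association with treatment failure. The exclusions also cut off the severe end (saturation below 90%, danger signs, MUAC below 115 mm), which limits how prognostic some measures can be.
- **That listing them as subgroups shows they predict failure.** Those objectives pose effect modification as an open question, which is a different matter from prognosis.
- **That the omission leaves a flaw through chance imbalance.** Under randomization the planned interval already allows for it.

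**Conclusion.** The point holds as a minor efficiency suggestion. The reason given for gender does not address the primary endpoint, and baseline values of two endpoint components are available but unused. Under assumed AUCs of 0.61 to 0.70 the fixed-design gain is 0.3 to 1.1 percentage points of power and 0.01 to 0.05 points of interval half-width, less any overlap with age. Even the top of that range would change the conclusion only in a borderline result. The case for the change rests on its low cost and on the structural link between the measures and the endpoint. It does not rest on any prognostic strength shown in the documents.

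**What to change.** Before unblinding, amend SAP 6.1 and 7.3 to add to age, site and gender:
- baseline oxygen saturation, temperature and age-standardised respiratory rate, as continuous terms;
- malaria result and wheeze, as yes/no terms.

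In the same edit:
- state whether respiratory rate is taken before or after bronchodilator, since wheezing children are reassessed after it;
- state whether MUAC is included;
- fill the rare missing baseline value with the overall mean;
- align protocol 5.1, which adjusts for age only;
- check that the matching variables in SAP 8 are consistent with the enlarged model.

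If the sponsor prefers the present set, one sentence justifying gender for treatment failure would be enough.

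The cost is a slightly longer model and minor edits to the imputation and protocol text. No new data are needed, and 1,900 children with about 150 failures (8% of 1,900 = 152) can support the extra terms. The linear model with robust standard errors remains valid under randomization and still estimates a rate difference.
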